**Fig. 2 Fig2:**
[figure not shown]
Timeline of post-resuscitation management and follow-up. This schematic outline illustrates the temporal progression of key clinical interventions following ROSC or initiation of ECLS. Early actions such as coronary angiography, targeted temperature management, and LV unloading might occur within the first days. Intermediate evaluations, including clinical examination, and EEG or MRI in patients who remain comatose, are emphasized at least 5–7 days after ROSC. Clinical examination will be assessed at 30 days, 90 days and 180 days after cardiac arrest. Long-term strategies incorporating GDMT, device therapy or advanced therapy might be considered for survivors with heart failure. CPC: cerebral performance category; ECLS: extracorporeal life support; EEG: electroencephalogram; GDMT: guideline-directed medical therapy; LV: left ventricular; MRI: magnetic resonance imaging; mRS: modified Rankin scale; ROSC: return of spontaneous circulation

#### Study endpoints

The primary endpoint is defined as 30-day survival with Cerebral Performance Category (CPC) score of 1 or 2). The CPC score will be assessed by the designated neurologists at each participant hospital, who are blinded to the intervention received. Secondary endpoints include favorable neurological status (modified Rankin scale (mRS) < 3, crude survival and neurologically favorable survival at discharge, 3 months, and 6 months; duration of mechanical ventilation; duration of stay in ICU; duration of hospitalization; causes of hospital mortality and late mortality; and health care costs. The incidence of serious adverse events related to CPR, ECMO, coronary angiography, and LV unloading will be documented as safety endpoints.

For patients still hospitalized at 30 days, bedside assessment is performed. For discharged patients, assessment is conducted during scheduled follow-up clinic visits or via structured telephone interview using validated instruments.

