## Introduction

### Global burden of out-of-hospital cardiac arrest

Out-of-hospital cardiac arrest (OHCA) is a global public health burden, characterized by the high mortality, the potential for long-term disability, and the strain on healthcare systems. The incidence of emergency medical services (EMS)-treated OHCA has been reported as 40.6 per 100,000 person-years in Europe, 47.3 in North America, 45.9 in Asia, and 51.1 in Australia [1]. Hospital survival after OHCA varies substantially by region, and a global survival rate is estimated to be around 8 to 10% [2].

OHCA is a highly time-sensitive medical emergency whose outcome is heavily impacted by prompt resuscitation and intervention before irreversible organ damage develops. Early recognition of OHCA and activation of the emergency response system, and immediate initiation of cardiopulmonary resuscitation (CPR) result in a doubling or even tripling of survival rates of OHCA [3]. For individuals experiencing OHCA with shockable rhythms (e.g., ventricular fibrillation (VF) and pulseless ventricular tachycardia (pVT)), early defibrillation is the key action to further improve the chances of survival [4]. According to the International Liaison Committee on Resuscitation (ILCOR) survey in 2025, survival to hospital discharge or 30-day survival after EMS-treated OHCA and bystander-witnessed shockable OHCA ranged from 3.1% to 20.4% and from 11.7% to 47.4%, respectively [1].

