### Extracorporeal cardiopulmonary resuscitation for refractory OHCA

Refractory cardiac arrest, defined as the failure to achieve sustained return of spontaneous circulation (ROSC) despite prolonged CPR efforts or multiple defibrillation attempts, is associated with an even worse prognosis [5]. It is estimated that greater than 70% of patients with shockable OHCA are refractory to conventional CPR and remain pulseless on arrival at the emergency department (ED) [6]. Extracorporeal cardiopulmonary resuscitation (ECPR) is the application of extracorporeal membrane oxygenation (ECMO) or extracorporeal life support (ECLS) in patients with refractory cardiac arrest, aiming to immediately reconstitute the cardiopulmonary function outside patients’ bodies and thus buy time for the delivery of interventions necessary to regain an adequate native circulation [7]. As the most efficient approach of resuscitation for refractory cardiac arrest, the number of ECPR runs has increased tenfold over the last decades [8]. Multiple observational studies have supported the use of ECPR in refractory OHCA [9]. Encouragingly, in expert institutions with highly dedicated and well-trained ECPR teams, a > 40% functionally intact survival of refractory OHCA could be achieved [9, 10]. However, recent randomized controlled trials (RCT) have reported seemingly inconsistent results of ECPR for refractory OHCA [11–13]. Latest update on Adult Advanced Cardiovascular Life Support (ACLS) from the ILCOR Consensus on Science With Treatment Recommendations recommendation assigns a IIa recommendation for use of ECPR in patients with cardiac arrest refractory to standard ACLS [14].

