### Statistical analysis

#### Sample size rationale

The trial is designed to demonstrate a treatment effect on the primary endpoint. Accepting a power of 80% and a level of significance of 5%, the sample size is calculated using a two-sided chi-square test. In reference to published multicenter trials, we estimate a 30-day neurologically favorable survival of 25% and 12% in the emergency total ECLS group and the standard ACLS with rescue ECMO group, respectively. Assuming a 10% dropout rate, we plan to enroll 186 participants per arm (roughly 200). No interim analysis is planned. If interim analysis is deemed necessary determined by Consortium committee, we will conduct one interim analysis 1 year after enrollment, and the statistical testing will be adjusted to this accordingly. The flowchart of intention to treatment and per protocol are attached in supplement.

All patients enrolled in the study will be analyzed primarily on an intention-to-treat basis. Continuous variables will be reported as mean ± standard deviation or median with interquartile range. Categorical variables will be presented as frequency. A logistic regression model with the stratification variable (center) will be conducted to evaluate the primary efficacy endpoint by treatment group. Odds ratios are to be calculated as effect estimates with 95% confidence intervals. Patients whose primary outcome cannot be assessed will be regarded as failures.

Per-protocol analysis, which only includes patients who adhere to the allocated protocol, will be performed to minimize the impact of non-adherence or deviations from the strict protocol.

For patients randomized to the total ECLS group, if ECPR is not required due to stable ROSC at ED or ECMO is initiated after 20 min since arriving at ED or after 60 min since emergency calls, they would be excluded from per-protocol analysis. Similarly, for patients randomized to the standard ACLS with rescue ECMO group, if ECMO is initiated within 20 min of arriving at the ED or within 60 min of emergency calls, they would be considered crossover and excluded from per-protocol analysis.

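### Raw durations of ventilation, ICU stay and hospitalisation, named as secondary endpoints without accounting for death, have no consistent direction as measures of recovery and are likely, though not certain, to look longer in the arm that saves more lives

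*Protocol article*

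**What the plan says.** The Study endpoints section of the protocol article lists, among the secondary endpoints, "duration of mechanical ventilation; duration of stay in ICU; duration of hospitalization". They are plain durations. The same list contains "crude survival and neurologically favorable survival at discharge, 3 months, and 6 months", causes of death and health care costs.

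The Statistical analysis section puts all enrolled patients into a primary intention-to-treat analysis and summarises continuous variables by mean with standard deviation or median with interquartile range. Unassessable outcomes count as failures, but that rule is written for the primary outcome only. For the primary endpoint the design assumption reads "we estimate a 30-day neurologically favorable survival of 25% and 12% in the emergency total ECLS group and the standard ACLS with rescue ECMO group," in that order. The Cost-effectiveness analysis section counts ICU and hospital stay among direct medical costs.

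The caption to Figure 1 describes a narrower final analysis set. This point takes the intention-to-treat statement as governing.

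**The concern.** The primary endpoint builds death into its definition. The three durations do not. A patient who dies in the emergency department has zero or undefined ICU time, and a patient who dies on the ward has a hospital stay that ends at death. On this scale a low value is good if it reflects recovery and bad if it reflects death, so the scale has no fixed direction.

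That matters because the trial is designed to change survival. If the strategy works, more patients in the total ECLS arm live long enough to build up ventilator, ICU and hospital days, and the arm can appear slower to recover when it is not. A strategy that only turned early deaths into later ones would move the durations the same way. Restricting the comparison to survivors does not solve this, because survivors are a subset formed after randomisation that the treatment is meant to enlarge.

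At stake is the reading of three secondary endpoints. The primary analysis is unaffected.

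**Working it through.** **Plan's own figure.** The article gives no expected length of stay, no timing of deaths and no target difference for the durations, so there is nothing to reproduce. The stated sample size of 186 per arm concerns the primary endpoint. It is used below only to set a simulation size.

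**Inputs from the article**
- Favourable 30-day survival (CPC 1 or 2): 25% and 12% (Sample size rationale).
- Background survival: "bystander-witnessed shockable OHCA ranged from 3.1% to 20.4% and from 11.7% to 47.4%, respectively", the second range being for the bystander-witnessed shockable group. Refractory arrest "is associated with an even worse prognosis" (Introduction).
- Neuroprognostication no sooner than 5–7 days after ROSC, with withdrawal of care only after it is complete, so some deaths among admitted patients are not early.

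**Assumptions, not in the article**
- 25% and 12% stand in for survival. True survival is higher by the share alive with CPC 3–4. A programme cited in the Discussion had 55% hospital survival and 50% with good neurological outcome, a gap of 5 points, but in a different setting.
- Mean stay is Ls in survivors and Ld in non-survivors, the same in both arms, so recovery does not differ.

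**Mean duration.** With survival s, mean = s × Ls + (1 − s) × Ld. Between arms:

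shift = (0.25 − 0.12) × (Ls − Ld) = 0.13 × (Ls − Ld)

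| Ls / Ld (days) | Total ECLS | Standard ACLS | Shift |
|---|---|---|---|
| 20 / 3 | 7.25 | 5.04 | +2.21 |
| 15 / 2 | 5.25 | 3.56 | +1.69 |
| 10 / 5 | 6.25 | 5.60 | +0.65 |
| 8 / 8 | 8.00 | 8.00 | 0 |
| 5 / 10 | 8.75 | 9.40 | −0.65 |

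The formula is for the mean. The median was not worked out.

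**How often the better arm looks longer.** Simulated with 167 per arm (186 × 0.9), gamma stays (shape 2) in survivors, exponential stays in non-survivors and 600 runs per scenario. The arm with more survivors had the longer mean in about 98% of trials at 20/3 and 15/2, 96% at 10/3 and 65% at 10/8.

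**How much faster recovery would hide the shift.** Let survivors in the total ECLS arm stay f × Ls. Setting 0.25 × f × Ls + 0.75 × Ld = 0.12 × Ls + 0.88 × Ld gives

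f = (0.12 × Ls + 0.13 × Ld) / (0.25 × Ls)

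so f = 0.56 (20/3), 0.55 (15/2), 0.64 (10/3) and 0.90 (10/8). At 20/3, survivors would have to stay 44% less before the raw means even tied.

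**Ambiguity of direction.** Suppose survival is 12% in both arms and non-survivors stay 5 days instead of 3 under total ECLS. The mean rises by 0.88 × 2 = 1.76 days with no extra survivor, close to the 1.69 days produced by a 13-point survival gain at 15/2.

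**Event-free days to day 30, death scored 0.** With fixed stays the difference is 0.13 × (30 − Ls): +1.3 days at Ls = 20 and +2.6 at Ls = 10, in favour of the life-saving arm. In the simulations, including those with shortened survivor stays, it favoured that arm throughout, by about 1.6 to 3.6 days. On these inputs 75% and 88% of patients score 0, so both medians are 0.

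**The case against.** The strongest reply is that a journal article lists endpoint names and leaves their handling to the full protocol or analysis plan, which are not shown. The sentence on means and medians is generic reporting, no between-arm test of the durations is specified, and nowhere is a shorter stay called better. This stands in part: a missing analysis rule is not a finding here, and the direction is the reader's. What remains is the choice of variable. The article names raw durations as endpoints, and no later choice of test gives that scale a direction.

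Second, crude survival and causes of death are reported beside the durations, so a longer stay can be read in context. A reader could suspect the cause, but could not separate more survivors from slower recovery.

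Third, the durations have a legitimate use. A reader might infer that they say nothing about resource burden. The article does not support that: ICU and hospital stay enter the cost analysis, and for costing, raw days per randomised patient, deaths included, is the relevant quantity. A longer stay because more patients live is then a real cost.

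Fourth, a reader might infer that most patients die early and that the better arm must look worse on all three endpoints. The article gives no timing of death, the complement of 25% and 12% includes survivors with CPC 3–4, and prognostication at 5–7 days or later makes some deaths late. The shift can also differ between the three endpoints. This objection stands against certainty, but not against the ambiguity.

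**Conclusion.** As efficacy or recovery measures, the three raw durations have no consistent direction, and under the design's own rates they are likely, not certain, to look longer in the arm that saves more lives. The artefact in the mean is about 0.13 × (Ls − Ld): +0.65 to +2.2 days for assumed stays of 10/5 to 20/3, nil at equal stays, and reversed if non-survivors stay longer. This rests on the planned favourable-survival rates standing in for survival and on assumed lengths of stay. It does not extend to the primary endpoint or to the durations as resource-use data. The change is worth making because it is cheap.

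**What to change.** For efficacy, replace the three durations with ventilator-free days, ICU-free days and days alive out of hospital, counted from randomisation to a fixed day in all randomised patients, with death in the window scored 0 or given the worst rank. Day 30 matches the primary endpoint. A longer window may suit hospital days, since the article expects some patients to be in hospital at day 30. An alternative is time to discharge alive with death as a competing event.

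Because most patients will score 0, compare means or ranks rather than medians, and show mortality and the separate components alongside. Keep the raw durations as descriptive and cost data, overall and by survival status, without reading them as recovery.

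The cost is mainly endpoint wording. The durations, survival status and readmissions are already to be recorded, and the sample size does not change. The downside is that free-day scores weight death by convention and partly repeat the mortality result.

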### Statistical analysis

#### Sample size rationale

The trial is designed to demonstrate a treatment effect on the primary endpoint. Accepting a power of 80% and a level of significance of 5%, the sample size is calculated using a two-sided chi-square test. In reference to published multicenter trials, we estimate a 30-day neurologically favorable survival of 25% and 12% in the emergency total ECLS group and the standard ACLS with rescue ECMO group, respectively. Assuming a 10% dropout rate, we plan to enroll 186 participants per arm (roughly 200). No interim analysis is planned. If interim analysis is deemed necessary determined by Consortium committee, we will conduct one interim analysis 1 year after enrollment, and the statistical testing will be adjusted to this accordingly. The flowchart of intention to treatment and per protocol are attached in supplement.

All patients enrolled in the study will be analyzed primarily on an intention-to-treat basis. Continuous variables will be reported as mean ± standard deviation or median with interquartile range. Categorical variables will be presented as frequency. A logistic regression model with the stratification variable (center) will be conducted to evaluate the primary efficacy endpoint by treatment group. Odds ratios are to be calculated as effect estimates with 95% confidence intervals. Patients whose primary outcome cannot be assessed will be regarded as failures.

Per-protocol analysis, which only includes patients who adhere to the allocated protocol, will be performed to minimize the impact of non-adherence or deviations from the strict protocol.

For patients randomized to the total ECLS group, if ECPR is not required due to stable ROSC at ED or ECMO is initiated after 20 min since arriving at ED or after 60 min since emergency calls, they would be excluded from per-protocol analysis. Similarly, for patients randomized to the standard ACLS with rescue ECMO group, if ECMO is initiated within 20 min of arriving at the ED or within 60 min of emergency calls, they would be considered crossover and excluded from per-protocol analysis.

Subgroup analysis will be undertaken to evaluate the treatment effect in subgroups of patients defined by.age (> 50 vs ≤ 50 years): Older age is associated with worse OHCA outcomes; treatment benefit may differ by age.Gender: Biological and healthcare access differences may influence ECPR outcomesTime from emergency call to ED arrival (< 30 min, 30–45 min, vs 45–60 min): Low-flow time is critical for neurological outcomes; treatment effect may be time-dependentST-segment elevation on ECG: Marker of acute coronary occlusion; patients with STEMI may benefit more from rapid reperfusionInitial lactate level (< 10 vs ≥ 10 mmol/L): Marker of metabolic derangement and tissue hypoperfusion; may predict treatment responsivenessInitial pH (< 7.0 vs ≥ 7.0): Marker of severe acidosis; extreme acidosis may limit treatment benefit.

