**Fig. 1 Fig1:**
[figure not shown]
Study flowchart. Before arriving at ED, the eligibility of OHCA patients will be evaluated by the OHCA response team of the receiving hospital, based on on-scene information provided by EMS. For eligible OHCA patients, randomization will be completed within 5 min of arrival at ED. After CT imaging, patients of first enrollment will be checked again if any exclusion criteria are met. Only patients who received early coronary angiography and/or intervention will be included in the final analysis. ACLS: advanced cardiovascular life support; CCL: cardiac catheterization laboratory; CPC: cerebral performance category; CPR: cardiopulmonary resuscitation; CT: computed tomography; ECLS: extracorporeal life support; ED: emergency department; EKG: electrocardiography; EMS: emergency medical services; mRS: modified Rankin scale; OHCA: out-of-hospital cardiac arrest; ROSC: return of spontaneous circulation; ECG: echocardiography

Randomization is performed immediately upon ED arrival (target: within 5 min) for patients meeting inclusion criteria and experiencing refractory cardiac arrest (defined as ongoing CPR on arrival). Patients with stable ROSC before randomization (defined as sustained pulse with systolic BP ≥ 90 mmHg without ongoing chest compressions for ≥ 2 min) are not randomized and proceed directly to coronary angiography.

Patients with unstable ROSC defined as: (1) return of pulse but requiring ongoing chest compressions, (2) recurrent VF/VT requiring repeated defibrillation, (3) persistent profound hypotension with systolic BP < 90 mmHg or mean BP < 60 mmHg despite vasopressor support, or (4) intermittent epinephrine injection to maintain the heart beating are eligible for randomization."

A computerized randomization list is provided by the National Taiwan University Hospital Clinical Trial Center by a software app (REDCAP). The randomization is in 1:1 ratio, stratified by participant hospitals, with a permuted block of 4. In-hospital randomization is conducted by OHCA response team coordinators immediately after the eligible patients arrive at ED. The randomization codes will be maintained by the National Taiwan University Hospital Clinical Trial Center and monitored by the Data Safety Monitoring Committee. The EMS teams and intensivists in the cardiac intensive care unit (ICU) will be blinded to the study group assignment and follow the institutional standards for post-cardiac arrest care.

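### The stated sample size of 186 per arm does not follow from its stated inputs, which give 155; the surplus is unexplained but conservative

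*Protocol article*

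**What the plan says.** All inputs and the result stand in the protocol article, under Sample size rationale, except the allocation ratio, which is given with the randomization procedure.

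- Power and significance: "Accepting a power of 80% and a level of significance of 5" per cent.
- Test: "the sample size is calculated using a two-sided chi-square test". No continuity correction is mentioned.
- Rates: "we estimate a 30-day neurologically favorable survival of 25% and 12% in the emergency total ECLS group and the standard ACLS with rescue ECMO group".
- Allocation: "The randomization is in 1:1 ratio, stratified by participant hospitals, with a permuted block of 4".
- Interim looks: "No interim analysis is planned". The next sentence lets the consortium committee add one, but gives no inflation of the sample size for it.
- Result: "Assuming a 10% dropout rate, we plan to enroll 186 participants per arm (roughly 200").
- Handling of missing primary outcomes in the intention-to-treat analysis: "Patients whose primary outcome cannot be assessed will be regarded as failures".

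**The concern.** The paragraph supplies everything needed to recompute the target, so a reader can check it, and the check fails. This is not a detail that a condensed article leaves to a fuller document: inputs and result are both printed and do not agree.

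Readers will use the stated rates and power to judge what a null result excludes. If the printed power is not the power of the printed design, that judgement starts from the wrong figure. The target is also given as 186 and, in the same sentence, as about 200 per arm.

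The allowance for loss and the analysis also treat losses differently. Dividing by 0.9 supposes that lost patients leave the denominator. The primary analysis keeps patients with an unassessable outcome and scores them as failures, which leaves the sample intact and shrinks the difference.

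**Working it through.** **Inputs.** p1 = 0.25, p2 = 0.12, difference 0.13, mean rate p̄ = 0.185; two-sided α = 0.05 (z = 1.960); power 80% (z = 0.8416); 1:1 allocation; dropout 10%.

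**Step 1: the plan's own figure.** Standard formula for the chi-square test:

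n = [z_α √(2p̄(1−p̄)) + z_β √(p1(1−p1) + p2(1−p2))]² / (p1−p2)²

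- First term: 1.960 × √(2 × 0.185 × 0.815) = 1.0763
- Second term: 0.8416 × √(0.1875 + 0.1056) = 0.4556
- n = (1.0763 + 0.4556)² / 0.0169 = 138.9, so 139 evaluable per arm
- Enrolled: 139 / 0.9 = 154.4, so **155 per arm** (310 in total)

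The plan has 186, which is not reproduced. The gap is 186 − 155 = 31 per arm, or 31/155 = 20%.

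**Step 2: could the choice of formula explain it?** Same α, sidedness, power, rates and dropout:

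| Method | Evaluable per arm | Enrolled per arm |
|---|---|---|
| Unpooled variance | 137 | 153 |
| Arcsine | 137 | 153 |
| Pooled variance in both terms | 141 | 157 |
| Log odds ratio | 146 | 163 |
| Exact power, Fisher or Yates | about 152 | about 169 |
| Continuity-corrected | 154 | 172 |

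The largest is still 14 per arm short of 186.

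**Step 3: which inputs would give 186?** Several would, each departing from the text:

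- 25% vs 12%, 90% power, no dropout: 185.4, so 186
- 25% vs 13%, 80% power, 10% dropout: 167 / 0.9 = 185.6, so 186
- 25% vs 12%, 80% power, 25% loss: 139 / 0.75 = 185.3, so 186
- 25% vs 12%, 85% power, log odds ratio formula, 10% dropout: 167 evaluable, so 186

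Matching the integer does not identify the cause.

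**Step 4: power that the planned numbers deliver at the stated rates.**

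Power = Φ{ [(p1−p2)√n − 1.960 √(2p̄(1−p̄))] / √(p1(1−p1) + p2(1−p2)) }

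- 186 per arm, no loss: (0.13 × √186 − 1.0763) / 0.5414 = 1.287, power **90.1%**
- 10% removed, 186 × 0.9 = 167: (0.13 × √167 − 1.0763) / 0.5414 = 1.115, power **86.8%**
- 10% scored as failures: the rates become 0.9 × 25% = 22.5% and 0.9 × 12% = 10.8%, difference 0.117, n stays 186: (0.117 × √186 − 1.0326) / 0.5203 = 1.082, power **86.0%**

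For the rounded figure of 200 per arm, power is 92.0% with no loss. With 10% scored as failures it is (0.117 × √200 − 1.0326) / 0.5203 = 1.196, or 88.4%.

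**Step 5: the two targets.** 2 × 186 = 372 and 2 × 200 = 400, a difference of 28 patients.

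**The case against.** The strongest reply is that nothing is lost: the trial enrols more than its inputs need, and at the stated rates it exceeds 80% power however the 10% is handled. That stands, and it limits the severity.

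A second reply is that every printed input may be as intended, with a further allowance left out of a condensed article. Table 1 lists exclusions after randomization, and the per-protocol text discusses crossover; either could have prompted extra patients. This also stands as a possibility. A reader might infer that a stated rate, power or dropout figure must be wrong, but the article does not support that.

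A reader might also infer that the true control rate was 13%, and hence that power falls just below 80% once missing outcomes count as failures (79.2% at 22.5% vs 11.7%). The 13% figure appears nowhere in the article. It is one of several back-solved values and should be used neither as a correction nor as evidence of underpowering.

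The failure rule is a small matter. Dropout is not defined, and losses from exclusions after randomization or from refused deferred consent might in fact leave the analysis. At the stated rates the two treatments of loss differ by 86.8% − 86.0% = 0.8 percentage points.

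Finally, 186 is an explicit number and the 200 in parentheses may be loose rounding. That is fair, but 28 patients is too wide a gap to leave as rounding.

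None of these replies makes 186 follow from the paragraph as printed.

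**Conclusion.** The point holds as a moderate error of reporting and traceability. The stated inputs give 155 enrolled per arm, or 172 at most under the standard variants tried, against a planned 186. An input is misstated or an allowance is unstated; the article does not settle which.

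The discrepancy is conservative if 25% and 12% are the intended rates: power is about 86% to 87% after 10% loss, not the 80% stated. The 86.0% figure assumes that all of the 10% are unassessable outcomes, equally frequent in both arms and unrelated to the true outcome. All the power figures are for the unadjusted chi-square test used in the sample size calculation, not for the centre-adjusted logistic model of the primary analysis.

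**What to change.** Rewrite the sample size paragraph from the original calculation:

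- State the rates, power, loss allowance and formula actually used, and name any extra allowance (for example, for exclusions after randomization or crossover).
- If 25% vs 12% and 186 per arm stand, restate the power as about 86% with 10% unassessable outcomes counted as failures, and 90% with none.
- Say what dropout means, and compute the allowance in line with the failure rule where it refers to missing outcomes.
- Give one target, either 372 or 400 in total, and remove the alternative.

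The control rate should not be changed merely because another value reproduces 186. The cost is one corrected paragraph, and the registry entry if it is affected. No patients are added, and the conduct and analysis of the trial do not change.

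### The primary model adjusts for centre only; prespecifying age and call-to-ED time as covariates would be a cheap, minor improvement

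*Protocol article*

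**What the plan says.** The Sample size rationale part of the Statistical analysis section names the model and its single adjustment variable: "A logistic regression model with the stratification variable (center) will be conducted to evaluate the primary efficacy endpoint by treatment group". The effect measure follows: "Odds ratios are to be calculated as effect estimates with 95% confidence intervals". No other covariate and no adjusted supportive analysis is named.

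The section on enrollment and randomization stratifies 1:1 allocation by hospital, in permuted blocks of 4. The abstract gives eight centres. Neither age nor time is a stratification factor.

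The subgroup list in the Statistical analysis section gives a reason for each subgroup. For age it says "Older age is associated with worse OHCA outcomes". For the time from emergency call to ED arrival it says "Low-flow time is critical for neurological outcomes". The Introduction adds that the chance of good recovery falls quickly with each further minute of CPR. Age is cut at 50 and time is put in three bands (below 30, 30–45 and 45–60 min), for subgroup analysis only.

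**The concern.** The article argues that age and time matter for the outcome, and both vary widely among eligible patients: 18 to 75 years, and up to 60 minutes from call to arrival (Table 1). Both are settled before randomization, which takes place at ED arrival, and both must be collected for the subgroups. Yet neither the randomization nor the primary model controls for them.

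Two things are at stake. The first is some precision, because a covariate that predicts a binary outcome usually raises the power of the treatment test. The second is protection against chance imbalance. If one arm happens to be younger or to arrive sooner, the centre-only estimate carries that difference. Adjustment that is decided on after the imbalance has been seen is open to challenge.

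**Working it through.** **Inputs from the article.** Rates of 25% and 12%; two-sided 5% level; 80% power; 10% dropout; 186 per arm; eight centres; allocation stratified by hospital only.

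**Assumed, because the article does not give it.** Odds ratio per SD of 0.8, 0.7, 0.6 or 0.5 for each of age and call-to-ED time; the two independent; between-centre SD of 0.3 on the logit scale.

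**1. The plan's own figure.** The article says that "the sample size is calculated using a two-sided chi-square test". With pooled rate 0.185:

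n = [1.960·√(2·0.185·0.815) + 0.842·√(0.25·0.75 + 0.12·0.88)]² / 0.13² ≈ 138.9, so 139 per arm, and 139/0.9 gives 155 after dropout.

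This does not reproduce 186. With a continuity correction it is 154, or 172 after dropout. The 90%-power size before any dropout allowance is exactly 186. That is a separate matter, but it bears on this one: centre-only power starts from about 90% (90.1% at 186 per arm; 86.8% at 167, which is 186 less 10%), not from 80%.

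**2. Power with and without the two covariates.** 8,000 simulated trials per setting, eight equal centres, marginal rates held at 12% and 25%, both models fitted to each trial, Wald test at 1.96. A centre with no events was left out of that trial's fit. 184 per arm is the equal-centre size nearest to 186.

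| OR per SD (each) | 184 per arm | 168 per arm | 136 per arm |
|---|---|---|---|
| 0.8 | 90.8% → 91.3% | 89.2% → 89.4% | 81.2% → 81.3% |
| 0.7 | 90.7% → 91.6% | 88.0% → 89.0% | 80.5% → 81.7% |
| 0.6 | 90.5% → 92.4% | 87.7% → 89.8% | 80.1% → 82.8% |
| 0.5 | 90.4% → 93.2% | 88.3% → 91.6% | 80.3% → 84.3% |

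The gain at 184 per arm is 0.5 to 2.8 points. The Monte Carlo SE of one power figure is about √(0.9·0.1/8000) = 0.3 points, so the smallest gains should be read as close to none. With covariates of no effect (odds ratio 1; 3,000 trials, 184 per arm) power was 90.2% for both models.

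**3. Type I error.** Under no treatment effect, with odds ratio 0.5 per SD and 184 per arm: 4.6% centre-only and 5.1% adjusted. Both are acceptable.

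**4. Chance imbalance.** The approximate shift in the unadjusted log odds ratio from a 1.96-SE imbalance in one covariate is |ln OR|·1.96·√(2/n). At n = 167 per arm:

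- OR 0.8: 0.223·1.96·0.109 = 0.048
- OR 0.5: 0.693·1.96·0.109 = 0.149

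The design log odds ratio is ln[(0.25/0.75)/(0.12/0.88)] = 0.894. Its SE is √[1/(167·0.1875) + 1/(167·0.1056)] = 0.298. The shift is therefore 5% to 17% of the design effect, and at most half an SE. At 186 per arm it is 0.045 to 0.141, or 5% to 16%. Under randomization, an imbalance this large in a given covariate is expected in about one trial in 20.

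**5. Cost in events.** Expected events: 186·0.25 + 186·0.12 = 68.8. Parameters beside the intercept: treatment 1, centres 7, covariates 2, so 10. That is about 6.9 events per parameter, against 68.8/8 = 8.6 for the centre-only model.

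**The case against.** The strongest reply is that the chosen model is sound. It adjusts for exactly the factor used in stratification, holds its type I error and exceeds the power target. A richer model is then a preference, and further covariates may be in an analysis plan that is not shown. Most of this stands: there is no error to correct. But the article does state the primary model and its one adjustment variable, so this is a choice open to comment. If an analysis plan adds covariates to the primary model, the two documents need to be aligned.

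The adjustment also has a price. There are fewer events per parameter, linearity is assumed for two covariates, a rule for missing values is needed, and the adjusted odds ratio is a different conditional quantity from the centre-only one. All of that stands.

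A reader might infer more than the article supports:

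- **That the plan calls these factors strong predictors.** It does not. Age is said only to be associated with outcome. The stronger wording is about low-flow time, of which call-to-ED time is only a part. Both remarks are given as reasons for subgroups.
- **That ROSC state at randomization should also be a covariate.** It is used for eligibility, but nothing says that it is recorded as a variable or calls it prognostic. One definition of unstable ROSC includes ongoing compressions, so it overlaps with ongoing CPR.
- **That an odds ratio is wrong because the trial was sized on proportions.** 25% against 12% is simply an odds ratio of 2.44, so the two are compatible.

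Table 1 repeats the age limits among its post-randomization exclusions, so age may not be confirmed within the first five minutes. It remains a baseline characteristic and can be established later without bias.

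**Conclusion.** The point holds as a low-cost improvement of minor weight. The centre-only model is valid and is not underpowered for the stated rates. Prespecifying age and call-to-ED time would mainly insure against an imbalance that hospital stratification does not control. The power gain is secondary, and its size rests entirely on assumed covariate strengths: near zero for weak covariates, approaching 3 points at about 186 per arm if each has an odds ratio of 0.5 per SD. Describing that gain as free would overstate it. The larger gain at 136 per arm (up to 4.0 points) belongs to a smaller trial than the one planned.

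**What to change.** Before any unblinded data are seen, prespecify the primary logistic model as treatment, centre, age and call-to-ED time. Keep both covariates continuous rather than using the subgroup cut-points. State how a missing covariate value is handled, without reference to arm, so that no randomized patient is dropped.

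Beside the odds ratio, report a risk difference standardized over the trial population, with a 95% confidence interval. It is on the same scale as the 13-point planning difference (25% − 12%), and it avoids comparing conditional odds ratios from different models. Keep the centre-only model as a named sensitivity analysis.

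The cost is a few sentences in the analysis plan and matching wording in the protocol. No new data are needed, because the planned subgroups already require both variables. If about 7 events per parameter is thought too thin, prespecifying the adjusted model as supportive is a reasonable fallback.
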